## Abstract

**Introduction:**

This article outlines the rationale and methodology of the ENERGY expenditure of COmmuting to school study (the ENERGYCO study), a cluster-randomized controlled trial. The ENERGYCO study is divided into two phases: Phase I will aim; to assess the physical activity energy expenditure (PAEE) of different modes of commuting to school (i.e., walking, cycling, and motorized-vehicle) using indirect calorimetry in Spanish adolescents; and Phase II will aim to assess the effect of a school-based cycling intervention on resting metabolic rate and PAEE, as well as on other physiological, physical, and psychosocial outcomes on Spanish adolescents.

**Method:**

For Phase I, a convenience sample of ~50 adolescents will be recruited. These participants will have their PAEE assessed in three different modes of commuting. Regarding phase II, a total of 300 adolescents from different schools in three Spanish cities will participate in this cluster randomized controlled trial. As many schools as necessary to meet the target sample will be included. In addition, each school will be randomized as either an intervention or control group. Participants from intervention schools will be asked to complete a school-based cycling intervention, while participants from control schools will be asked to continue their same habits for 8 weeks. The school-based cycling intervention will last for 8 weeks and will include *Bikeability* sessions, along with encouragement strategies to increase adherence to cycling to and from school.

**Conclusion:**

The ENERGYCO study will provide novel insights into the PAEE associated with different modes of commuting to school using indirect calorimetry, as well as a comprehensive overview of how an 8-week school-based cycling intervention impacts resting energy expenditure, daily energy expenditure, and the physical and psychosocial health of adolescents.

## Introduction

1

Resting metabolic rate (RMR) constitutes the primary component of 24-h energy expenditure, representing the energy requirement for sustaining bodily functions while at rest in thermoneutral conditions (1). Given, fat-free mass (FFM) serves as a robust predictor of RMR in adolescent population (2, 3), exercise-induced weight loss is an important research topic since it leads to increases RMR by increasing the fat free mass component (4). However, studies in the adolescent population to modify the RMR have focused mainly on resistance or aerobic exercise (5, 6), without taking into account how regular physical activity (PA) might affect the RMR. Understanding PA energy expenditure (hereinafter referred to as PAEE) as the result of any muscular movement due to PA (7), the interaction of intensity, duration, and frequency of PA determines the total PAEE. In that sense, the American College of Sports Medicine states that exercise and health-oriented PA should be performed consistently to obtain its associated benefits. Nevertheless, nowadays there is an energy imbalance in the youth population, with high energy intake and low PAEE (8). This fact may have led to an increase in obesity in the young population worldwide, by 5.6% in girls and 7.8% in boys between 1975 and 2016 (9). In fact, the World Health Organization (WHO) has considered the overweight and obesity as a global public health concern (10). Although overweight and obesity have a multifactorial origin (9, 11), the literature recommends increasing PAEE through regular PA, as it is the most easily modifiable component of 24-h energy expenditure (11), to address the current situation. Therefore, interventions targeting young populations should aim to increase PAEE to restore or maintain energy balance (12).

In this regard, given that the young population commutes to and from school at least twice on a school day, promoting active modes of commuting, mainly walking or cycling (13), has been considered as an effective strategy to improve their health (14). Indeed, scientific evidence shows that active commuting to and from school (ACS) is associated with higher levels of total PA (15), during weekdays (16), and it even appears that those adolescents who walk to school also are more active in other contexts (17, 18). In fact, such is its impact on PA levels, that in the meta-analysis conducted by Campos-Garzón et al. (19), they indicated that actively commuting to and from school may help to complete 48% of the PA recommendations in young population. Nevertheless, few studies have analyzed the PAEE related to ACS (12, 20) and to the best of our knowledge, no study has analyzed how ACS impact on RMR. Moreover, while it is well known that walking and cycling are active modes of commuting to school, they can provide different health benefits (14). Cycling to school could be more related to physical fitness and physiological improvements such as, increasing in cardiorespiratory fitness levels and overall health (14), contributing to reducing the risk of cardiovascular diseases, obesity, diabetes or depression (14, 21–24). Therefore, although ACS has several associative benefits, it is important to know the differences between walking and cycling when promoting it (25).

Despite the limited number of studies analyzing PAEE related to ACS, a significant gap remains in accurately assessing PAEE during free-living behaviors. Indirect calorimetry is widely recognized as the gold standard for measuring PAEE, as it directly quantifies oxygen consumption and carbon dioxide production, providing continuous, real-time data that capture the complex metabolic responses during activity (26). This direct measurement offers a significant advantage over methods that rely on predictive equations or self-reported data, which often oversimplify the dynamic and context-specific nature of free-living behaviors (26). Previous studies have frequently relied on stationary or semi-portable indirect calorimetry systems that are not well-suited for field applications (27). Although portable metabolic systems have been developed to facilitate outdoor assessments, their high cost and operational complexity limit their widespread use in educational and field contexts (27). As an alternative, researchers have employed established equations, such as those proposed by Riebe et al. (28) and Pandolf et al. (29). However, these equations were derived under highly controlled laboratory conditions (e.g., typically on treadmills) and, consequently, do not account for the variability of environmental factors (e.g., changes in speed, terrain, and weather), which critically influence PAEE in real-life settings, particularly in ACS (30). Another common practice for analyzing PAEE related to ACS has been through estimates based on counts measured by accelerometers (20, 31). However, accelerometers may not be the most appropriate devices for measuring PAEE in the context of ACS (32). Moreover, a recent study compared the PAEE associated with walking to that of using an e-scooter (33). However, this study was conducted under laboratory conditions, making it impossible to account for environmental factors that could influence PAEE. It is well known that the availability of safe and accessible routes directly correlates with increased PA among adolescents, which could, in turn, lead to higher PAEE (34). Additionally, PA levels may depend on adolescents’ perceptions in their commuting environment, considering factors such as fear of accidents, infrastructure, and social norms related to active commuting behaviors (35). Therefore, it is crucial to compare the PAEE associated with different modes of commuting to school in free-living conditions. Furthermore, developing a context-specific equation that incorporates key commuting characteristics (e.g., speed and distance) would provide a more accurate estimation of PAEE associated with this behavior.

Furthermore, ACS interventions have primarily been conducted in children (i.e., from 6 to 11 years) rather than in adolescents (i.e., from 12 to 17 years) as well as promoting walking rather than cycling. These interventions have primarily focused on changes in the mode of commuting, frequency of commuting, or increased PA levels (36–39) rather than assessing the effects on 24-h energy expenditure components (i.e., RMR and PAEE). In addition, interventions to improve RMR or PAEE have mainly consisted of resistance or endurance trainings (5, 11), being these activities performed out of school. To the best of our knowledge the effect of a school-based cycling intervention on the RMR and daily PAEE of adolescents has not been studied to date. In fact, the assessment of the effects of a school-based cycling intervention could be particularly important to consider as a suitable strategy to increase the RMR and re-balance PAEE in the adolescent population. In addition, a school-based cycling intervention will not only produce effects at physiological level (i.e., RMR or PAEE), but it will also allow to deepen the effects of this mode of commuting to school at physical or psychosocial level in the adolescent population. It has been shown that cycling to school is associated with greater grip strength and vertical jump (40), but the association does not imply causality. Similar results occur at the psychosocial level, where cycling to school has been associated with greater well-being or increased social relations compared to use passive passively commuting to school in adolescents (41). Moreover, there is controversy as to whether cycling to school could improve young people’s body composition (14). Thus, a school-based cycling intervention is needed to increase and improve the evidence of the effects of cycling to school in physiological, physical, and psychosocial outcomes.

Therefore, this protocol describes the rationale and methodology of the ENERGY expenditure of school Commuting study (The ENERGYCO study). ENERGYCO project will address the gaps and limitations in the existing scientific literature regarding the PAEE that occurs during cycling to school. Considering the previous literature and existing gaps, the ENERGYCO project will be divided into two phases. Phase I will focus on using a portable metabolic system to assess PAEE associated with different modes of commuting (i.e., walking, cycling, motorized vehicles) under free-living conditions in Spanish adolescents. Additionally, Phase I will serve to develop a predictive equation that will be used in Phase II to measure PAEE associated with different modes of commuting to and from school. Additionally, considering the ongoing debate regarding the health benefits of ACS and the scarcity of studies examining the effects of school-based cycling interventions on RMR and PAEE, the Phase II will aim to assess the effects of a school-based cycling intervention on RMR and PAEE, as well as on other physiological (i.e., basal heart rate, blood pressure, and body temperature), physical (i.e., PA levels, anthropometric measures, body composition, physical fitness, and motor competence), and psychosocial outcomes (e.g., perceived barriers to active commute to school, self-esteem, and mental health) on Spanish adolescents. It is hypothesized that, in Phase I, using a portable metabolic system under free-living conditions will provide accurate and distinct measurements of PAEE associated with different commuting modes in Spanish adolescents. Specifically, we hypothesize that these measurements will highlight significant differences in PAEE across commuting modes, offering a more precise understanding of how commuting impacts adolescents’ physical activity levels. Additionally, we expect the data collected in Phase I to contribute to the development of a valid and reliable predictive equation for estimating PAEE during commuting to and from school. we hypothesize that a school-based cycling intervention will lead to a significant increase in both RMR and PAEE compared to a control group. We further hypothesize that the intervention will improve physiological outcomes (e.g., reductions in basal heart rate), physical outcomes (e.g., enhanced physical fitness and motor competence), and psychosocial outcomes (e.g., increased self-esteem) among Spanish adolescents.

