### Study population

2.2

In the Phase I of the ENERGYCO study, a convenience sample of 50 students (12–16 years old) will be recruited to assess the PAEE of different modes of commuting to school (i.e., walking, cycling, and motorized-vehicle). For Phase II, the ENERGYCO study will recruit a random sample of students (*n* = 300) from the three Spanish cities (i.e., Granada, Almería, and Jaén). The intervention aims to assess the effects of a school-based cycling intervention in the RMR and PAEE related to cycling to school, as well as its impact on others physiological, physical, emotional, and psychosocial outcomes in Spanish adolescents. The randomization process is presented in Figure 1.

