
**Table 1 tab1:** Schools’ inclusion and exclusion criteria.

Inclusion criteria	Exclusion criteria
The school has a specific space for parking bicycles and allows their parking	The school does not have specific infrastructure to park or store bicycles
The school has at least two classes per grade	The school offers bus transportation to the adolescents
At least eight students from the school will agree to participate in the study	The school is already participating in other interventions focused on promoting healthy behaviors
Schools from urban areas	The school has implemented an intervention to encourage commuting to school within the last year
	Schools from rural areas

**Table 2 tab2:** Participants’ inclusion and exclusion criteria.

Inclusion criteria	Exclusion criteria
Adolescents’ females and males aged from 12 to 17 years old (both ages included)	Adolescents younger than 12 years or older than 17 years
Healthy participants who can ride a bicycle safely and without difficulty.	Participants with any injury or medical condition that prevents safe participation in cycling to and from school
Be able to cycle to and from school at least 3 days per week during eight consecutive weeks (Intervention group)	Insufficient ability to ride a bicycle or inability to cycle to and from school at least 3 days a week (Intervention group)
Not to cycle to and from school more than 3 days a week during the last year	Participants who have cycled to and from school more than 3 days a week during the past year
To present a valid signed consent from their parents or legal guardians	Participants without a valid, signed parental or guardian consent form
To present valid data at baseline and follow-up from all the outcomes assessed	Participants who do not provide valid data for all assessed outcomes at baseline and follow-up

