##### Energy expenditure related to active commuting to school

2.7.1.2

PAEE related to different modes of commuting to school (i.e., walking, cycling, passive modes) will be measured using the Cosmed K5 portable metabolic system in Phase I. The Cosmed K5 has previously shown a good level of agreement compared to stationary metabolic carts at low cycling intensity (5.8% difference in VO_2_). At moderate intensities, it slightly underestimated VO_2_, VCO_2_, and energy expenditure (~6.6–6.9%). Additionally, during walking tests, the Cosmed K5 demonstrated high reproducibility, with a coefficient of variation of 4.5% for energy expenditure per kilometer and a concordance coefficient of 0.91. VO_2_ measurements were consistent, with low variability in the fraction of expired oxygen (coefficient of variation of 0.9%) (56). The Cosmed K5 is worn on the back with a harness and measures oxygen consumption (VO_2_) and carbon dioxide production (VCO_2_) in breath-by-breath mode. Before each assessment, the device will be calibrated using a reference gas mixture of 15.92% O_2_ and 5.03% CO_2_. Delay calibration for the breath-by-breath mode will also be performed (57). During the test, participants will breathe normally while commuting, and the Cosmed K5 will record data continuously. Data will be analyzed as the mean VO_2_ and VCO_2_ (ml/min) during each commuting mode. In Phase II, PAEE related to cycling will be estimated using predictive equations developed in Phase I. These equations will incorporate variables such as distance, speed, and heart rate, and will be cross-validated against PAEE measurements obtained with the Cosmed K5 to ensure accuracy. Therefore, data will be analyzed as the mean VO_2_ and VCO_2_ (ml/min) during each cycling trip to and from school, aggregated by participant during the intervention period.

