#### Statistical analysis

2.10.2

Descriptive analyses of all study variables presented with the mean (standard deviation) and frequencies (percentage) will be performed. Subsequently, the normality of the variables will be analyzed using histograms and normality tests. In Phase I, for the comparison of PAEE between the different modes of commuting (i.e., walking, cycling, and motorized-vehicle), a repeated measures ANOVA will be performed using the per-protocol approach. In addition, Student t-test or Mann–Whitney tests will be performed to compare the fluctuation of PAEE according to speed or distance commuted between active modes of commuting (i.e., walking vs. cycling).Within Phase II, the effects of the school-based cycling intervention on RMR and other health-related outcomes will be studied using an analysis of covariance (ANCOVA). Post-intervention RMR and other-health related values will be included as dependent variables, group (i.e., experimental group vs. control group) as fixed factor, and baseline outcome data as covariates. To evaluate the effect of the intervention on the secondary outcomes (i.e., physiological, physical, and psychosocial outcomes), we will conduct the same analysis used for the main outcomes (i.e., ANCOVA analysis using the intention-to-treat approach). Moreover, to control the variability between schools, the analyses will include adjustments for contextual and organizational variables, such as the SES of the school area, the length of cycling lanes, the availability of bicycle parking, and the level of engagement of teachers and students in the intervention. The estimates will be present as raw and standardized (z-scores; i.e., mean differences between follow-up and baseline data divided by the standard deviation), as an indication of the change the post-intervention z-scores will be calculated relative to the baseline mean and standard deviation. Effect sizes will be categorized as small (0.2 SDs), medium (0.5 SDs), and large (0.8 SDs), based on Cohen (93). Finally, to analyze the influence of covariates on the association between the intervention and the main outcomes (i.e., RMR and PAEE), mediation analyses will be performed. The intervention will be included as the independent variable, and the main outcomes as the dependent variables. Covariates included in the mediation analysis will encompass body composition, physical function, cognitive determinants, perceived barriers or autonomy, built-environment characteristics, weather, among others. In the statistical analysis, a value of *p* < 0.05 will be considered statistically significant.

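### Phase II PAEE is predicted from an equation fitted on about 50 adolescents but analysed as if measured, so its interval is too narrow when the arms differ and its standardised effect is not comparable with those on measured outcomes

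*Protocol article*

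**What the plan says.** Table 3 and section 2.7.1 make energy expenditure a primary outcome beside resting metabolic rate (RMR). The Introduction says that "Phase I will serve to develop a predictive equation that will be used in Phase II to measure PAEE", and section 2.7.1.2 repeats it: "In Phase II, PAEE related to cycling will be estimated using predictive equations developed in Phase I". On the inputs it says that "These equations will incorporate variables such as distance, speed, and heart rate". The development sample is described in section 2.2: "a convenience sample of 50 students (12–16 years old) will be recruited to assess the PAEE of different modes of commuting to school". Section 2.7.1.2 promises cross-validation against the portable calorimeter, then says that the Phase II values are analysed as gas-exchange means for each cycling trip, although no gas exchange is measured on those trips.

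Section 2.10.2 sets the Phase II model as an ANCOVA: "Post-intervention RMR and other-health related values will be included as dependent variables". Group is the fixed factor and the baseline value a covariate. The same section names RMR and PAEE as the main outcomes. Effects are also standardised, as "mean differences between follow-up and baseline data divided by the standard deviation", with follow-up z-scores referred to the baseline mean and SD, and are graded at 0.2, 0.5 and 0.8 SD. Section 2.10.1 plans sensitivity analyses for missing data only.

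**The concern.** A regression prediction differs from a measurement in two ways that matter here.

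- **Shared error.** Every Phase II value uses the same estimated coefficients. If the slope from 50 adolescents is 10% too steep, every predicted contrast is 10% too large. Recruiting more pupils in Phase II does not reduce this error, and the ANCOVA standard error does not contain it. Cross-validation tells the team how accurate the equation is. It does not put that inaccuracy into the Phase II interval.
- **Reduced spread.** Predictions vary less than the quantity they predict. A standardised effect that divides by their SD is on a different scale from one on a directly measured outcome, yet both are graded against the same cut-offs.

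At stake is the stated precision of a primary outcome, and how its effect reads beside the others.

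**Working it through.** The article gives no R², residual SD or interval width for the equation, so there is no figure of its own to reproduce. R² is an assumption and is shown as a range.

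**Inputs**
- n₁ = 50 in Phase I (section 2.2).
- n₂ = 125 per arm: 250 required, allocated 1:1 (section 2.4.2).
- d = 0.5: the planning effect size f = 0.25 in section 2.4.2, with d = 2f for two equal groups.
- Assumed: R² = 0.5, 0.7 or 0.8; the effect passes entirely through the predictors; no clustering and no baseline covariate; true PAEE scaled to SD 1.

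**Case A: both arms predicted by one equation.** The intercept error cancels between arms and the slope error remains.
- Variance that the analysis reports: 2R²/n₂.
- Variance left out: the slope has sampling variance (1 − R²)/n₁ and multiplies an arm difference of d/√R² in the predictor, giving d²(1 − R²)/(R²n₁).
- Ratio of true to reported SE: √(1 + left out/reported). Coverage: 2Φ(1.96/ratio) − 1.

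| R² | reported | left out | SE ratio | coverage |
|---|---|---|---|---|
| 0.5 | 0.0080 | 0.0050 | 1.28 | 88% |
| 0.7 | 0.0112 | 0.0021 | 1.09 | 93% |
| 0.8 | 0.0128 | 0.00125 | 1.05 | 94% |

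A simulation of this case (5,000 replicates) gave 86%, 93% and 94%; a second gave about 87%, 92% and 94%. At d = 0 the left-out term is zero and coverage is 95%. At d = 1.0 the formula gives 71%, 86% and 90%.

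**Case B: controls have no cycling PAEE.** Nothing cancels, so the error in the predicted mean level counts in full. Assume a mean of 100 and SD of 25 among cyclists, an effect of 100/25 = 4 SD. The reported variance is R² × 625/125. The left-out variance is about (1 − R²) × 625/50.
- R² 0.5: 2.50 and 6.25; SE 1.58 reported, √8.75 = 2.96 true; coverage 71%.
- R² 0.7: 3.50 and 3.75; 1.87 against √7.25 = 2.69; 83%.
- R² 0.8: 4.00 and 2.50; 2.00 against √6.50 = 2.55; 88%.

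A simulation with two predictors (4,000 replicates), which also carries the slope error, gave reported SEs of 1.59, 1.88 and 1.99, true SEs of 3.05, 2.76 and 2.57, and coverage of 69%, 81% and 87%. Even at R² 0.5 the effect lies 100/3.05 ≈ 33 true SEs from zero.

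**Standardised effect.** Predictions from a calibrated equation have SD √R² times the true SD, so the effect is multiplied by 1/√R² = 1.41, 1.20 and 1.12. If a fraction b of the true effect does not pass through the predictors, the factor is (1 − b)/√R². For b = 0.3 this is 0.99 at R² 0.5 and 0.78 at R² 0.8. For b = 0.5 it is 0.71 and 0.56.

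**The case against.** **The test is sound.** A reader might infer that the p-value for PAEE is invalid. It is not: with no arm difference in the predictors, the coefficient error multiplies zero. In Case B, where undercoverage is worst, the effect is so far from zero that the decision cannot change. This stands, and it limits the point to the interval and the standardised effect.

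**Inflation is not certain.** A reader might also infer that the standardised effect is bound to be too large. The article does not support that. Its z-scores use the baseline SD, and regular cyclists are excluded at entry, so a baseline SD may mix modes of travel; the R² that then matters could be higher and the inflation smaller. Heart rate is an equation input, and the Introduction expects basal heart rate to fall. If heart rate at a given oxygen uptake fell too, the equation would under-predict in the intervention arm. The direction is therefore open, although the lack of comparability remains.

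**Conditioning on an equation is common practice, and details can sit in an analysis plan.** Maximal oxygen uptake is also estimated from a published equation, and RMR has an equation as its contingency. So the comparison with measured outcomes should be limited to those that are directly measured. But the article itself fixes the predicted outcome, the model and the standardisation, and here the sponsor holds the development data, so the omission is easily repaired.

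**PAEE's place in the ANCOVA is inferred.** The model sentence names RMR and other health-related values only, and section 2.7.1.2 states no control or baseline PAEE value. However, section 2.10.2 calls PAEE a main outcome and says that secondary outcomes get the same ANCOVA as the main ones. The unstated control value is why two cases are shown.

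**Table 3 marks the portable calorimeter for both phases.** Taken alone, this would make Phase II PAEE a measurement. The Introduction and sections 2.1 and 2.7.1.2 say otherwise, and the table should be reconciled with them.

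**Conclusion.** The point holds in a limited form. The PAEE interval omits the Phase I coefficient error and is too narrow whenever the arms differ in the predictors. At d = 0.5 with both arms predicted, the loss is modest: coverage of about 86–88% at R² 0.5, 92–93% at 0.7 and 94% at 0.8. It reaches about 69%, 81% and 87% only if controls have no cycling PAEE. The type I error at zero effect is unaffected. The standardised PAEE effect is not comparable with effects on directly measured outcomes: it is inflated by up to 1/√R² if the equation is calibrated and captures the whole effect, and may be deflated otherwise.

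These sizes rest on assumed values of R², on the 25% coefficient of variation in Case B, and on ignoring schools and baseline adjustment. School-level variation in the reported SE would make the omission relatively smaller; a useful baseline covariate would make it relatively larger. This is a cheap improvement to the reporting of a primary outcome, not a flaw that overturns its test.

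**What to change.** In section 2.10.2:
- State that PAEE intervals come from a two-stage bootstrap: resample Phase I adolescents with all their bouts, refit the equation, recompute Phase II PAEE, resample schools and refit the Phase II model. Multiple imputation that draws the equation's coefficients and residuals is an alternative.
- Report the equation's R² and residual SD.
- Report the PAEE effect in raw units, or standardise it by the predicted SD with the equation's residual variance added back. If PAEE is averaged over many trips, the full residual variance is an upper limit for that correction.
- Do not standardise by the SD of the Phase I simulations. They last a fixed 15 minutes in a convenience sample and do not reflect the spread of real commutes. Do not apply the 0.2/0.5/0.8 grading to the uncorrected value.
- Reconcile the energy expenditure row of Table 3 with section 2.7.1.2.

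Neither resampling nor imputation repairs a wrong equation. Phase I covers ages 12 to 16 and Phase II admits 17-year-olds, so that extrapolation needs its own caveat.

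Cost: analysis wording, some scripting and a wider PAEE interval. Both data sets are the sponsor's own, and data collection does not change.
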